### Exclusion criteria

Individuals may not enter the study if they have any condition which might make participating in the physiotherapy or exercise regimes unsafe or confound results. People with the following will therefore be excluded:

1. Severe unstable cardiovascular or pulmonary disease.

2. Significant psychiatric or neurological conditions.

3. Bone loss secondary to other metabolic bone disorders or disease will be excluded (for example, rheumatoid arthritis, cancer, osteomalacia).

4. Individuals whose primary problem is back pain with pain radiating into the lower limb.

5. Individuals who have had a vertebroplasty, facet joint injection or any physical therapy (for example, chiropractic, osteopathy or physiotherapy treatment) for back pain in the previous 12 weeks. However, individuals who have had back pain and any of these treatments prior to this period will be eligible.

### Procedures

#### Recruitment

Potential participants will be approached by clinicians during their routine clinic attendance. Clinicians treating potentially eligible participants for the trial will introduce the study, hand out an invitation pack and obtain consent for a Physiotherapy Rehabilitation for Osteoporotic Vertebral Fracture (PROVE) trained researcher to make contact 3 to 7 days later. Participants consenting to enrol in the study will undergo a baseline assessment; following this the assessor will telephone the independent randomisation centre.

#### Randomisation, blinding and allocation concealment

Randomisation will be performed by an independent statistician and implemented by the central telephone registration and randomisation service at the Warwick Clinical Trials Unit. Staff will register patients after confirming eligibility, consent and baseline assessment, thus ensuring allocation concealment.

Baseline and follow-up assessments will be performed by a blinded research physiotherapist. These staff will not be involved in delivering the treatment interventions. All data will be entered by a data entry assistant to ensure the research physiotherapists remain blind to treatment assignment. All study personnel involved in data entry, management and analysis will be blinded until the final analysis is complete. By virtue of the design it is not possible to blind the participants or the physiotherapists providing the treatment interventions [30].

After randomisation the Clinical Trials Unit will inform the research therapist at each site of a participant’s treatment allocation, and they will liaise with appropriate clinical staff to provide the correct intervention.

### Baseline assessment

After participants have been assessed for eligibility and consent has been gained, baseline assessment will be carried out. Questionnaires and physical assessment will be completed (both participant and assessor will be unaware of allocation at this appointment). The baseline measures are summarised in Table 1.

**Table 1 T1:** Summary of outcomes and assessment schedule

**Tests**	**Administered by**	**Week 0**	**Month 4**	**Month 6**	**Month 9**	**Month 12**
Functional Co-morbidities Index	Self	*√*				
QUALEFFO 41	Self	*√*	*√*	By post	By post	*√*
EQ-5D-5 L	Self	*√*	*√*	By post	By post	*√*
Physical Activity Scale for the Elderly	Self	*√*	*√*	By post	By post	*√*
Timed Load Standing	Assessing therapist	*√*	*√*			*√*
Flexicurve ruler	Assessing therapist	*√*	*√*			*√*
The Short Performance Physical Battery	Assessing therapist	*√*	*√*			*√*
The Functional Reach test	Assessing therapist	*√*	*√*			*√*
6 minute walk test	Assessing therapist	*√*	*√*			*√*
10 point visual analogue scale	Self	*√*	*√*			*√*

### Outcome measures

There are two primary outcomes for this study: one measure of QoL and one measure of physical function.

1. The QUALEFFO 41 is a disease-specific measure of health related QoL applicable to patients with established vertebral osteoporosis. It is a self-administered questionnaire that provides scores on five domains; pain, physical function, social function, general health perception, mental performance, and a total score. It is validated and reliable and has been shown to be responsive in clinical trials of physiotherapy treatment [31]

2. The Timed Loaded Standing (TLS) test assesses back extensor muscle endurance [32]. Based upon previous literature [9], a 2.6 second change in the TLS test would be clinically significant for a change between the groups.

The study sample size gives adequate power to detect a treatment effect in both the QUALEFFO 41 and TLS as described more fully below.

### Secondary outcomes

There are a number of outcomes included seeking to assess a number of different aspects of symptoms, function and activity. We will be piloting the package, and if the burden of measurement is too great, some measures will be dropped and the protocol amended.

The Functional Co-morbidities Index will be completed as other diseases are likely to be present in this older population which might affect physical outcomes [33].

Spinal curvature and flexed posture will be described by recording height (cm) and thoracic kyphosis. Thoracic kyphosis will be measured using a flexicurve ruler with the patient in a standing position to calculate an index and angle of kyphosis [34].

Other outcomes include measures of balance, mobility and physical activity. Each test is reliable and valid, has been used with older, community dwelling adults and shown to be responsive in previous rehabilitation studies.

•The Short Performance Physical Battery will be used to assess lower extremity physical function [35]. Poor performance is predictive of future disability, hospitalisation and care needs.

•The Functional Reach Test will be used to specifically evaluate standing balance and to act as a predictor of falls risk [36].

•A 6 minute walk at self-selected speed over a 30 metre course will be used to measure exercise endurance; an important parameter of functional, community mobility [37].

•The Physical Activity Scale for the Elderly is a short, self-administered questionnaire to assess activity in the past week [38].

•The EuroQol EQ-5D-5 L is a short, generic measure of QoL and will be completed to facilitate the assessment of cost-effectiveness and also to give a comparison with other clinical conditions [39].

•Participants will be asked to specifically rate back pain on activity and at rest using a 10 point visual analogue scale.

•Information about fractures and falls will be collected using a standardised definition and a prospective participant completed event calendar. These will be mailed to participants monthly during the year of the study and participants will be telephoned by the trial co-ordinator to promote adherence and to check this information is captured precisely [40].

### Follow-up data collection

Follow-up data collection will be by face-to-face clinical assessment at 4 and 12 months.

### Interventions

Treatments are standardised, but it is considered important to allow therapists to personalise treatments as appropriate. For example, therapists will be able to omit or adjust the intensity of any technique or exercise to reflect an individual participant’s capabilities and their progress.

#### Best practice usual care

Currently, relatively few patients are referred for formal physiotherapy for an osteoporotic vertebral fracture. Therefore, a single education session will form the usual care arm. The education will be general advice about osteoporosis, and lifestyle choices to promote bone health in line with the information available from the National Osteoporosis Society.

#### Active interventions

Participants in each active intervention group will be offered up to seven individual physiotherapy sessions over 12 weeks. A 12-week programme was chosen to allow time to progress the treatment intensity and achieve gains in strength and mobility [9,25]. This pragmatic regime allocates equivalent physiotherapist contact time to participants in each intervention group and broadly reflects current outpatient physiotherapy resources within the NHS. Alongside individual sessions, participants in each intervention group will receive education about osteoporosis and general advice about exercise.

##### Manual therapy intervention

Manual therapies will include low velocity spinal mobilisation performed without discomfort [8-10] and soft tissue mobilisation to erector spinae, rhomboids and upper trapezius muscles [9]. Postural taping will be used once weekly and, if tolerated, it will be worn continuously for 3 days for the first 4 weeks. It will be applied to create gentle skin traction and sensory feedback about posture when the individual moves into flexion [8,9,12]. The home programme will be a passive stretch that promotes thoracic extension for 15 minutes per day [4].

##### Exercise intervention

The exercise programme will include active stretches, progressive balance and strength training and low to moderate intensity weight-bearing aerobic activity (for example, walking). Exercises will be practised in the treatment sessions and continued in the home programme. The Rating of Perceived Exertion scale will be used to set the initial load of strength exercises and walking duration at a self-perceived moderate level of effort, to facilitate monitoring and allow structured progression. Participants will be asked to include short sessions of exercise within daily life, aiming to achieve a total of 60 minutes of exercise per day, three to five times a week depending on ability (for example, a 30 minute walk along with 30 minutes of stretches, balance and strengthening exercises [28]). Stretches will promote spinal extension, shoulder flexion, hip extension and ankle dorsiflexion [28]. Specific trunk extension and lumbar stabilisation exercises will be included [4,22,23]. There will also be upper body and lower body strengthening exercises [22,28] and specific balance exercises such as single leg standing [21,26]. Wherever possible exercises will use body weight and gravity to provide resistance and balance related activities to the programme (for example, sit to stand will be encouraged to increase proprioceptive input [20]). We will use a series of educational and motivational strategies to foster compliance: clinician-patient goal setting, the provision of an exercise diary with a log sheet to record sessions, along with a scheduled telephone call to support practice [41]. Completion of home practice will be monitored through exercise diaries and compliance will be defined as 60% completion. Participants undergoing the interventions will be encouraged to continue their home exercises at the end of the active phase of the trial. Figure 2 provides an overview of the interventions in each trial arm.

**Figure 2 F2:**
[figure not shown]
**Flowchart of interventions.** 4/12 f/u, 4- and 12-month follow-up.

### Adherence

Compliance with treatment will be defined as attending at least four treatment sessions. The number of physiotherapy visits and content of treatment sessions will be recorded using both therapist-completed treatment logs and patient exercise and participation diaries. Compliance of the physiotherapists to the treatment protocol will be assessed and monitored by analysis of the treatment logs and by site visits.

### Quality monitoring

There will be initial training provided to all PROVE trial assessors and clinicians involved in delivering the intervention at all sites. Once the training has been completed the following procedures are in place to promote consistency and high quality trial procedures across all sites:

•A member of the PROVE team will observe each assessor perform one of their first assessments to ensure they take place as per protocol. Repeat visits will be undertaken should any concerns arise until reliable and valid assessments occur.

•Within 2 weeks copies of all assessment forms will be sent to the trial co-ordinator for checking to identify any issues concerning missing data or poorly completed forms. Any issues or concerns will be discussed with individual assessors.

•A member of the PROVE team will observe each clinician perform one of their first treatments to ensure all treatments adhere to the protocol.

•Clinicians will be asked to complete a treatment log for each attendance, providing an approximate estimation of the time spent on key intervention components and detailing and explaining any deviations from the protocol.

•A member of the PROVE team will check each site’s trial master file and meet with researchers and clinicians from each site on an annual basis (or more frequently should this be necessary). During these meetings, feedback will be sought regarding trial procedures and the perceived acceptability of the intervention. Feedback will be documented and a copy of the minutes of the meeting will be returned to each site.

### Health economics

An economic evaluation is designed as an integral part of the trial and will take the form of a cost-utility analysis conducted from an NHS and Social Services perspective. Health outcomes will be expressed as quality-adjusted life years (QALYs) by combining survival and EuroQol EQ-5D data collected from each participant to 12 months. The cost to the health service of providing current practice and each type of physiotherapy intervention will be estimated during the trial, and participants will provide information to 12 months on healthcare contacts (for example, visits to the General Practitioner, outpatient clinics, and inpatient admissions). Care provided by Social Services will be documented as well as any out of pocket costs incurred by participants.

### Qualitative study

The qualitative study will help to provide a picture of the issues facing participants with osteoporosis and vertebral fracture who participate in the treatment interventions arms of the study. Semi-structured interviews will be conducted by a researcher experienced in the design, collection and analysis of qualitative data. Specific topics covered will be exercising with osteoporosis (including adherence issues), and participant experience of the PROVE trial. We will interview enough participants to ensure we are confident that theoretical sufficiency will be achieved [42]. Purposive sampling will be used to achieve a sample which includes female and male patients, thoracic and lumbar single/multiple vertebral fracture patients and patients of varying activity levels. Fracture site, number of fractures and activity levels are known to influence outcome and, since the majority of research regarding osteoporotic patients’ QoL has previously been undertaken with women, it is considered important to capture the views of male participants within the current study.

Interviews will be conducted either in the hospital or participants homes following the completion of the intervention and the 4-month follow-up appointment. The development of the interview schedule will be iterative and the questions asked may develop and change as the interviews are conducted and analysed [43]. All interviews will be digitally recorded and fully transcribed for analysis. Analysis will utilise Smith’s experiential approach of Interpretative Phenomenological Analysis. A feature of Interpretative Phenomenological Analysis is that the first steps of analysis begin early in the research process with initial data coding and is simultaneous to data collection. Initial analysis of each interview will be carried out as soon after its completion as possible following the guidelines set out by Smith [43].

One in five of the interviews will be coded independently by a second member of the research team with experience of qualitative research to provide a different perspective on the coding. The research team will discuss the development of themes as the research progresses, once again with the aim of providing a different perspective and enhancing the development of themes.

### Data and statistical analysis

#### Interim analysis decision rules

The decision to adapt the trial following the interim analysis and whether to drop one of the treatment arms, or to continue, will be made by the Trial Steering Committee based upon the recommendations of the independent data monitoring committee (IDMC). The IDMC will base their decision on the data from the interim analysis, using the rules below, together with data on adverse events, falls and further fracture history. An interim analysis will be conducted when the 16-week follow-up data are available for 75 patients per treatment arm. The aim of this interim analysis is to terminate either the manual therapy or exercise therapy arm if it appears to be poorly performing relative to the other intervention or to the control, or to terminate the trial completely if both intervention arms appear to be performing poorly relative to the control.

Although the integrity of the trial in terms of type I error control does not require pre-specification of the decision rule to be used at the interim analysis, as a guideline for the IDMC the interim analysis decision rule will be based on comparison of the estimated mean change from baseline in the QUALEFFO score for each of the three study arms as follows:

a) If the mean change from baseline of the QUALEFFO score for an intervention arm is not more than 0.5 points greater than that for the control arm, that intervention arm will be dropped from the study. Note that under this rule both intervention arms might be dropped, in which case the study would stop due to futility.

b) If the mean change from baseline of the QUALEFFO score for one intervention group is more than 2 points higher than for the other group, the intervention with the lower mean change from baseline will be dropped from the study.

#### Sample size

The initial sample size calculation is based on a traditional approach to a three-arm trial. We wish to detect a standardised effect of 0.4 in the QUALEFFO; at 80% power and an alpha of 0.05 we would require 180 to 200 participants in each arm or 540 to 600 people (we will use 600 people as the upper limit).

A simulation study was conducted to estimate the power of the study assuming the interim decision rules above were used. The sample size for the interim analysis was chosen to be 75 per arm. This ensures that the power is high while the probability of continuing with an ineffective treatment is sufficiently low. If the true (unknown) treatment effect for an intervention is equal to the control, the probability of dropping that intervention at the interim analysis is approximately 73%. If neither intervention is truly superior to the control, the probability of stopping the entire study at the interim analysis is approximately 60%. Based on this interim analysis sample size the standard error of the estimated difference between the intervention arms and the control arm at the interim analysis will be 0.82.

In the adaptive design of the type proposed, the power of the study may be defined as the probability, given a truly effective intervention, that the intervention remains in the trial at the interim analysis and leads to a significant result in comparison to the control in the final analysis. The specified sample size gives 94% power if the better of the two intervention arms has a true standardised treatment effect of 0.4.

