### Statistical analysis

We will report according to CONSORT standards.

Regression models will be used to estimate the treatment effects (with 95% confidence intervals) and will be adjusted for important covariates (prior fracture history and age). The final statistical analysis will include data from patients from the control arm and intervention arm(s) continuing beyond the interim analysis from both the first and second stages of the trial. The analysis needs to allow for the adaptation made at the interim analysis in order to ensure that the probability of a type I error (false positive result) is controlled. It is proposed to use the analysis method described by Bretz and colleagues [44], applying a Dunnett correction to the comparisons between the intervention arms and the control arm at the first stage and at the second stage unless an intervention arm is dropped.

Complier-average causal effect will be estimated to assess the impact of adherence on the effect of the interventions.

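### The printed inputs (0.4 SD, 80% power, alpha 0.05) do not give 180 to 200 per arm; they need about 99, or 117 to 133 with a correction for two or three comparisons

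*Protocol article*

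**What the plan says.** The Sample size section of the protocol article gives two calculations.

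- The first is introduced with "The initial sample size calculation is based on a traditional approach to a three-arm trial". Its target is "We wish to detect a standardised effect of 0.4 in the QUALEFFO", and its result is that "at 80% power and an alpha of 0.05 we would require 180 to 200 participants in each arm or 540 to 600 people". The text adds that "we will use 600 people as the upper limit", which is 200 per arm. It states no loss allowance, no division of alpha and no sidedness.
- The second is a simulation of the adaptive design with the interim rules in force. The interim size is 75 per arm. Power is defined as the probability that an effective intervention both survives the interim look and is significant against control at the end. The result is that "The specified sample size gives 94% power if the better of the two intervention arms has a true standardised treatment effect of 0.4".

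The only multiplicity method that the article names is in Statistical analysis: "applying a Dunnett correction to the comparisons between the intervention arms and the control arm at the first stage", and also at the second stage unless an arm is dropped. It is not listed as an input to the 180 to 200.

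**The concern.** The first calculation prints its effect, power and alpha, and presents the number per arm as what those values require. A standardised effect of 0.4 is moderate, and at 80% power it usually needs about 100 per group. The printed figure is about twice that. The same section later gives 94% power for the same standardised effect, with no explanation of how the two statements relate.

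At stake is whether the stated basis for the 540 to 600 range can be checked. If a loss allowance or a stricter alpha is inside the 180 to 200, the reader needs to know it in order to judge a recruitment shortfall or higher loss than expected. If none is inside, the trial has far more power for 0.4 SD than the paragraph says.

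**Working it through.** **Inputs.** From Sample size: d = 0.4, power 80%, alpha 0.05, equal arms, 180 to 200 per arm. Two-sided testing is my assumption, because sidedness is not stated.

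**Step 1: number per arm.** For two means, n = 2(z₁₋α/₂ + z₀.₈₀)² / d², with z₀.₈₀ = 0.8416 and 2/d² = 2/0.16 = 12.5.

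| Basis | Critical value | n per arm (normal) | n per arm (t-test) |
|---|---|---|---|
| One-sided 0.05 | 1.645 | 12.5 × 2.486² = 77.3, so 78 | – |
| Two-sided 0.05 | 1.960 | 12.5 × 2.802² = 98.1, so 99 | 99.1, so 100 |
| Dunnett, two comparisons with control | 2.212 | 12.5 × 3.054² = 116.6, so 117 | – |
| Bonferroni, 2 tests (0.025) | 2.241 | 118.8, so 119 | 120.1 |
| Bonferroni, 3 tests (0.0167) | 2.394 | 130.9, so 131 | 132.3 |
| Bonferroni, 4 tests (0.0125) | 2.498 | 139.4, so 140 | 141.0 |
| Bonferroni, 6 tests (0.0083) | 2.638 | 151.4, so 152 | 153.1 |

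A three-group ANOVA needs 92 to 122 per arm, depending on how the means are spread. Requiring both interventions to be significant needs 122 unadjusted or 143 with Dunnett. No row reaches 180.

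**Step 2: power at the printed size.** Power = Φ(d√(n/2) − critical value).

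- n = 180: 0.4 × √90 = 3.795. Unadjusted, Φ(1.835) = 96.7%; Dunnett, Φ(1.583) = 94.3%.
- n = 200: 0.4 × √100 = 4.000. Unadjusted, Φ(2.040) = 97.9%; Dunnett, Φ(1.788) = 96.3%.
- With Bonferroni for three comparisons, the values are 91.9% and 94.6%.

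**Step 3: effect detectable at 80% power.** d = (critical value + 0.8416)√(2/n).

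- Unadjusted: 2.802 × 0.1054 = 0.30 at n = 180; 2.802 × 0.1000 = 0.28 at n = 200.
- Dunnett: 0.32 and 0.31.

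**Step 4: could loss to follow-up alone close the gap?** Loss needed = 1 − n/180 to 1 − n/200.

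- From 99: 45% to 51%.
- From 119: 34% to 41%.
- From 131: 27% to 35%.

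**Step 5: the 94%.** The article says "The sample size for the interim analysis was chosen to be 75 per arm" and that "the standard error of the estimated difference between the intervention arms and the control arm at the interim analysis will be 0.82". This implies SD = 0.82/√(2/75) = 5.02 points, so 0.4 SD is about 2.0 points. I simulated the two interim rules (an arm is dropped if its difference from control is 0.5 points or less; the lower intervention is dropped if the two differ by more than 2 points). The final test was a closed Dunnett test with inverse-normal combination, with 100,000 runs per scenario.

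My assumptions were: the better arm at 0.4 SD and the other at 0, 0.2 or 0.4; the same effect at 4 and 12 months; correlation between the two times of 1 or 0.6; second-stage places of a dropped arm either reallocated or not.

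- 600 people, no loss: 93.4% to 95.9%.
- 600 people, assumed 20% loss: about 89% to 94%.
- 360 people (120 per arm), no loss: about 79% to 86%.

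The stated 94% therefore reproduces at 600 people without loss. It also sits at the edge of the range with 20% loss, so the match does not prove which loss assumption the sponsor made.

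**The case against.** The best defence is that inputs are missing from the sentence and the arithmetic behind it is sound. The article condenses a fuller protocol, names two primary outcomes and has three pairwise contrasts of interest. Several coherent combinations do reach the range:

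- six tests with 15% loss: 153/0.85 = 180;
- six tests with 20% loss: 152/0.80 = 190;
- three tests with 30% loss: 131/0.70, so 188;
- 90% power with two tests and 20% loss: 156/0.80 = 195;
- 90% power at alpha 0.0125 with no loss: about 180.

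This stands as a possible explanation. It does not rescue the sentence, which prints a power and an alpha and says what they require. Each of these routes needs an allowance, an alpha split or a power that the section does not state, and the reader cannot tell which was used.

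It also stands that the first paragraph is not the only support for 600. The simulation of the adaptive design is a second one, and it reproduces.

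Three stronger readings are tempting and should be resisted.

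- **That 80% and 94% contradict each other outright.** The 94% has its own definition of power. The design also selects between arms and relaxes the Dunnett correction once an arm is dropped, so the two figures cannot be compared by a simple argument that a futility rule only loses power.
- **That the target is really about 0.3 SD.** The section states 0.4 twice and 0.3 nowhere. The 0.28 to 0.32 in the working is a back-calculation.
- **That the trial is underpowered.** The discrepancy runs the other way for QUALEFFO.

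**Conclusion.** The stated basis is wrong as written. The printed inputs need about 99 per arm unadjusted (about 300 people), 117 to 120 with a correction for two comparisons with control (351 to 360), and 131 to 133 for all three pairwise comparisons (about 400), against 540 to 600 printed. At the printed size the fixed-design power for 0.4 SD is about 97% to 98% unadjusted, or 94% to 96% with Dunnett.

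These figures assume a two-sided test, equal arms, no loss and no gain from covariate adjustment; a one-sided test or such a gain would widen the gap. Because the 94% is reproducible at 600 people, the fault most likely lies in the first paragraph. An unstated allowance remains possible and cannot be confirmed from the article. The consequence is limited: no analysis, error rate or decision rule depends on it, and the number recruited is more than enough for the printed QUALEFFO target.

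**What to change.** Rewrite the first paragraph of Sample size so that it can be reproduced, in one of two ways.

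1. Keep 180 to 200 per arm and correct the power: for 0.4 SD and two-sided alpha 0.05 with no loss, about 97% to 98% unadjusted, or 94% to 96% with Dunnett for two comparisons with control.
2. Keep the calculation and state the inputs actually used: power, sidedness, alpha and how it is divided among comparisons and outcomes, and the loss allowance.

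For the 94%, the sponsor should state from its own simulation record the analysed number per arm and the loss assumption. These should not be taken from the assumptions in this review, because the article does not say what the sponsor assumed.

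The cost is a few sentences. Recruitment stays at up to 600, and the interim rules and analysis do not change.
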